#### Exploratory outcome analyses

3.2.4

For the continuous patient-reported outcome scales, we will use linear mixed-effect models as described for the primary outcome.

We will evaluate complications after surveillance procedures and the number of invasive procedures as a count, that is, the number of complications per time under surveillance or the number of invasive procedures per time under surveillance. For these outcomes, we will use mixed effects and Poisson regression with a random intercept for each participant and the same fixed-effect model structure as described for the primary outcome.

For recurrence and progression, which are time to event, we will plot cumulative incidence curves, because this endpoint is subject to censoring by attrition. We will report cumulative incidence for each arm at 12 and 24 mo and compare incidence using a three-sample log-rank test. For consistency with the existing literature [17], time zero will be the time of each patient’s last tumor resection, and the time for any event will be the time of pathologically confirmed recurrence or progression. We will use the Fine-and-Gray approach to calculate proportional subdistribution hazards to address any competing risk of death [31].

Furthermore, we will estimate important feasibility data for a subsequent large noninferiority comparative effectiveness trial. We will use data from the data management and reporting system to estimate screening to enrollment ratios as well as dropout and crossover rates. Finally, we will plot patterns of recurrence and progression over time for the urine testing arms versus control, which will provide important preliminary data for powering the subsequent large noninferiority comparative effectiveness trial (Fig. 2). These longitudinal patterns are important to understand, as reporting of positive urine test results may make subsequent cystoscopy more sensitive because providers perform a more thorough evaluation after a positive test (Fig. 2C) [32]. This could signal an advantage of urine testing over control, but could lead to higher estimated recurrence rates in the urine testing arms, which would be hard to interpret without longitudinal data.

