#### Quality of life data (primary and exploratory outcomes) and complications (exploratory outcome)

2.6.1

The primary outcome is the patient-reported urinary quality of life domain score of the validated QLQ-NMIBC24 instrument, measured after surveillance. Exploratory outcomes include other QLQ-C30 and QLQ-NMIBC24 domains as well as anxiety and acceptability. These will be obtained by the clinical research coordinator via a phone survey 1–7 d after consent/randomization and after each surveillance visit via the general QLQ-C30 combined with the bladder cancer–specific QLQ-NMIBC24 [20], via the PROMIS Anxiety Scale [21], and via the Acceptability of Intervention Measure [22]. To encourage participation and to offset the burden of completing the quality of life surveys, participants will receive $20 per completed survey as a small token of appreciation for their time, effort, and inconvenience related to study participation.

For the purpose of collecting quality of life assessments, surveillance visits will be defined by the entire surveillance episode, which will include laboratory processing and communication of test results in the urine testing arms and, if applicable, also a cystoscopy triggered by a positive or nondiagnostic urine test.

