#### Surveillance discomfort (exploratory outcome)

2.6.3

The participant will be asked immediately after the cystoscopy or after providing a urine sample (depending on the arm and visit) to rate their discomfort on a visual analog scale ranging from 0 (no pain) to 10 (worst pain).

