### Study setting and recruitment

2.7

Consecutive patients, 18 yr and older, undergoing surveillance for low-grade intermediate-risk bladder cancer will be approached for participation if their first surveillance cystoscopy ≤4 mo after tumor resection shows no evidence for recurrence. We anticipate that the population for this study will include individuals with diverse demographic characteristics from three locations throughout the USA (Charleston, SC; Dallas, TX; and White River Junction, VT). The protocol allows for opening the study at additional sides as needed.

Each site’s principal investigator will present the study protocol to the appropriate local clinical care providers so that those involved in the care of potential participants are familiar with the protocol requirements. Each site will have at least one dedicated clinical research coordinator to facilitate enrollment.

Each site’s principal investigator and clinical research coordinator will work with the clinical care team to identify patients scheduled for surveillance cystoscopy ≤4 mo after tumor resection, who meet the study inclusion criteria. The screening and recruitment procedures will include tracking of all screened and approached patients according to the Screening, Eligibility, Approach, Randomization (SEAR) framework [24].

Electronic health data will be used to identify potentially eligible patients. Specifically, study teams will regularly review lists of patients scheduled for cystoscopy procedures and lists of patients who underwent recent bladder biopsy or transurethral resection. These patients will then be prescreened for potential eligibility by clinical research coordinators using the electronic health record, with data recorded as part of the SEAR framework described above. After preliminary consultation and eligibility assessment by a potential participant’s clinical team, the participating site’s clinical research coordinator will approach each patient immediately after their surveillance cystoscopy to discuss enrollment and informed consent (see the Supplementary material for model informed consent form). We anticipate recruitment of 240 participants over approximately 3 yr.

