### Randomization

2.8

A participant will be enrolled in the study once screened for eligibility and after providing written informed consent. After enrollment, the clinical research coordinator will enter the patient study ID number and stratification factors (site, sex, and receipt of prior intravesical therapy) into the secure online Research Electronic Data Capture (REDCap) system [25] to obtain a study arm assignment. The assignment will be based on the randomization lists provided by the statistician. The list of randomization with 1:1:1 allocation is stratified by site, sex, and receipt of prior intravesical therapy, and was created with permuted blocks of size 6. Receipt of intravesical chemotherapy is defined as treatment with bacillus Calmette-Guérin (BCG) or with intravesical chemotherapy in the 12 mo prior to enrollment.

The clinical research coordinator will then convey the assignment to the treating clinician and participant, and assist with scheduling surveillance visits according to study arm assignment. Given the pragmatic nature of this healthcare delivery study, the participants, clinical staff, and clinical research coordinators cannot be blinded to intervention assignment. However, we will assure that interventions are coded in a way that analytical staff will be blinded to interventions until the analysis phase for the primary outcome is completed.

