#### Primary outcome analyses: urinary quality of life

3.2.2

The primary outcome is the patient-reported urinary quality of life domain score of the validated QLQ-NMIBC24 instrument [20], measured as a repeated measure at each surveillance visit. We will model the primary outcome urinary quality of life in terms of the study arm and time using a mixed-effect model with a random intercept for the participant. We will include fixed effects for the study arm (indicators for the Xpert Bladder Cancer Monitor and the EpiCheck urine test with the frequent cystoscopy arm as the referent, ie*,* intent–to-treat analyses), for time points (3, 6, 12, 18, and 24 mo) as categorical variables (3-mo baseline as referent), and the interactions of the study arm and time point. The interaction provides information about the treatment efficacy and is analogous to a difference in difference. We will also add a fixed effect for sex as a biological variable, given that women’s urethras are much shorter than men’s, which may very well affect urinary quality of life after surveillance testing. Results from these models will be presented as adjusted means with standard deviations.

As a complementary analysis, we will employ a generalized estimating equation (GEE) with the same fixed effects and cluster with respect to the participant using an autoregressive 1 correlation structure. As another evaluation of the robustness of findings, we will repeat the mixed effects and GEE analysis above, removing the 3-mo baseline value from the longitudinal vector of urinary quality of life and instead add it as a covariate (fixed effect) and eliminate the interaction from the model; the information on efficacy from these complementary analyses is in the main effects for the study arm. If these complementary analyses do not confirm the findings from the primary analyses, we will explore the reasons for the divergent results and report these with our main study findings.

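### The inherited baseline-referenced model can shrink or cancel a real acceptability difference in its efficacy term, because the first acceptability rating is taken after participants know their arm

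*Protocol article*

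**What the plan says.** Section 2.6.1 of the protocol article lists the exploratory patient-reported outcomes: "Exploratory outcomes include other QLQ-C30 and QLQ-NMIBC24 domains as well as anxiety and acceptability". They are collected "via a phone survey 1–7 d after consent/randomization and after each surveillance visit", and acceptability is obtained "via the Acceptability of Intervention Measure". No separate timing is given for that instrument.

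Section 2.8 places disclosure of the arm directly after assignment: "The clinical research coordinator will then convey the assignment to the treating clinician and participant". The same section says that participants are not blinded.

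Section 3.2.4 fixes the analysis: "For the continuous patient-reported outcome scales, we will use linear mixed-effect models as described for the primary outcome". Section 3.2.2 describes that model as a random-intercept model with arm, categorical time (3-month value as referent), their interaction, and sex. On how to read it: "The interaction provides information about the treatment efficacy and is analogous to a difference in difference". Section 3.2.2 also says that results will be shown as adjusted means with SDs, and it adds complementary models in which the 3-month value becomes a covariate.

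**The concern.** A difference in difference is a sound treatment contrast when the reference value is unaffected by the arm. The Acceptability of Intervention Measure, as its name says, rates an intervention. Its first reading is taken when the participant already knows which surveillance programme lies ahead. If participants answer with that programme in mind, the reference value already contains part of the effect, and the interaction subtracts it. The term that the plan calls efficacy then answers whether acceptability moved between expectation and experience. It does not answer whether one programme is more acceptable than the other.

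An early difference is plausible on the article's own account. Section 1.3 reports that most patients undergoing cystoscopy would choose a urine test if it were proven safe, and that 68% of workshop participants thought avoiding even one cystoscopy worthwhile. At stake is a null or understated result on acceptability of surveillance, an outcome named in the abstract.

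**Working it through.** The article gives no figure for acceptability, so there is none to reproduce. The check is algebra followed by a simulation.

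**Algebra.** Let δ0 be the arm difference (urine test minus cystoscopy) at the first survey, δ6 and δ18 the differences at 6 and 18 months, and D = (δ6 + δ18)/2.

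- Interaction coefficients: δ6 − δ0 and δ18 − δ0.
- Their mean: D − δ0.
- With δ0 = f·D, the mean is D(1 − f).
- f = 0 gives all of D; f = 0.5 gives 50%; f = 0.8 gives 20%; f = 1 gives 0. If expectation exceeds experience (f > 1), the sign reverses.
- The direct contrast, arm main effect plus mean interaction, is δ0 + (D − δ0) = D for every f.

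**Simulation inputs.** From sections 3.1 and 3.2: 80 per arm, 20% missing at each time point, recurrence 10% per year, attrition 10% per year, exchangeable correlation 0.7, and 0.025 per comparison (taken as two-sided). The correlation is stated for the urinary score and is only assumed for acceptability. Both urine arms were given the same difference; 1,500 runs; differences in total SD units. Power means at least one urine arm significant. The contrast averages 6 and 18 months, as in the primary test.

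| True difference | Interaction estimate | Interaction power | Direct estimate | Direct power |
|---|---|---|---|---|
| 0.3 SD, stable from first survey (f = 1) | 0.00 | 4.7% | 0.30 | 55% |
| 0.6 SD, stable (f = 1) | 0.00 | 4.1% | 0.59 | 99% |
| 1.0 SD, stable (f = 1) | 0.00 | 5.0% | 1.00 | 100% |
| 0.6 SD, half present at first survey (f = 0.5) | 0.30 | 71% | 0.60 | 99% |
| 0.6 SD, none at first survey (f = 0) | 0.60 | 99.9% | 0.60 | 98.5% |

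In the stable rows the interaction rejects only at about its type I error rate. In the last row, the case most favourable to the plan, the direct contrast loses about one percentage point.

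**Precision.** The simulated standard errors were 0.127 (interaction) and 0.153 (direct), a ratio of 0.153/0.127 = 1.20. With complete data the variances, in SD² units, are:

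- Interaction: 2 × 1.5 × (1 − 0.7)/80 = 0.01125, so SE 0.106.
- Direct: 2 × [(1 + 0.7)/2]/80 = 0.02125, so SE 0.146.

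The two are equal when 1.5(1 − ρ) = (1 + ρ)/2, that is at ρ = 0.5. Simulated at 0.5 with the missing data, the direct contrast was the tighter one (0.149 against 0.162).

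**Baseline as covariate.** If the complementary model were carried over to acceptability, a stable difference d would appear as about d(1 − 0.7). Large-sample least squares with a single follow-up score gave 0.09, 0.18 and 0.30 for d = 0.3, 0.6 and 1.0. It shrinks the difference by about 70% but not to zero.

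**The case against.** The strongest reply is that the article does not say what the first acceptability rating refers to. Participants have just had the 3-month cystoscopy. If they rate that procedure, all arms rate the same thing, δ0 is near zero, and the interaction recovers most or all of D. The schedule of assessments is in Supplementary Table 2, which is not shown. This stands, and it is why the point is conditional. If that table omits acceptability at baseline, the condition fails in another way: the inherited model has no referent for this scale, and sections 2.6.1 and 3.2.4 need reconciling.

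Three further replies also stand in part. The adjusted means by arm would display a stable difference. The Wald test that averages 6 and 18 months is stated for the primary hypotheses and is not explicitly extended to exploratory scales. The fitted model already contains the arm main effect, so the direct contrast can be computed from it. But section 3.2.2 names the interaction as the term carrying efficacy, and section 3.2.4 adopts that model without exception.

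A separate analysis plan may treat this scale differently. The point is not that detail is missing; it is that the model the article does state suits this scale poorly.

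A reader might go further in two directions that the documents do not support:

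- That the discomfort scale has the same defect, because consent follows the 3-month cystoscopy. The coordinator "will approach each patient immediately after their surveillance cystoscopy to discuss enrollment and informed consent", so a rating at that encounter is feasible, and whether one is scheduled depends on the unseen table.
- That no baseline could serve a scale that rates an intervention. A score taken before randomization has zero expected arm difference, so the difference in difference would then equal the full post-visit contrast. The difficulty is the timing of the first rating.

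**Conclusion.** The point holds conditionally. The article applies to acceptability a model whose efficacy term removes any arm difference already present at a survey taken after open-label assignment. The loss is the share f of the true difference: none at f = 0, half at f = 0.5, all at f = 1. The value of f is unknown and cannot be derived from the documents. The power figures also rest on borrowing the urinary score's correlation of 0.7.

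A reader might infer that a real acceptability difference would be hidden altogether. That is too strong: a zero interaction requires a fully stable difference, and the means by arm would still show it. What can go wrong is the formal effect estimate and its test. Acceptability is exploratory, and the conclusion on urinary quality of life does not depend on it.

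**What to change.** State for acceptability that the effect is the direct between-arm difference in post-visit scores averaged over 6 and 18 months. It can be obtained as arm plus interaction from the planned model, or from a model of the post-visit scores without the 3-month referent. Report the post-assignment score descriptively only.

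The cost is about one sentence and no new data. The interval may be slightly wider: about 20% at a correlation of 0.7, with no penalty at 0.5 or below.

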## Abstract

“Replace Cysto” is a multisite randomized phase 2 trial including 240 participants with low-grade intermediate-risk non–muscle-invasive bladder cancer, in which participants will be randomized 1:1:1 to one of two urine marker–based approaches alternating a urine marker test (Xpert Bladder Cancer Monitor or Bladder EpiCheck) with cystoscopy or to frequent scheduled cystoscopy. The primary objective is to determine whether urinary quality of life after surveillance is significantly improved in the urine marker arms. The primary outcome will be the patient-reported urinary quality of life domain score of the validated QLQ-NMIBC24 instrument, measured 1–3 d after surveillance. Exploratory outcomes include discomfort after surveillance, the number of invasive procedures that participants undergo per 1000 person years, complications from these procedures per 1000 person years, nonurinary quality of life, acceptability of surveillance, and bladder cancer recurrence and progression. Comparators include surveillance using (1) the Xpert Bladder Cancer Monitor test, (2) the Bladder EpiCheck urinary marker, or (3) frequent cystoscopy alone. After a negative cystoscopy ≤4 mo following bladder tumor resection, all the participants will undergo surveillance at 6, 12, 18, and 24 mo (with time zero defined as the date of the most recent bladder tumor resection). In the urine marker arms, surveillance at 6 and 18 mo will be performed with the marker. Regardless of the arm, participants will undergo cystoscopy at 12 and 24 mo. End of study for each participant will be their 24-mo cystoscopy. Overall trial duration is estimated at 5 yr from when the study opens to enrollment until completion of data analyses. The trial is registered at clinicaltrials.gov (NCT05796375).

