### Objective and outcomes

2.3

The primary objective is to determine whether urinary quality of life during surveillance is improved in the urine testing arms. We chose the primary outcome, patient-reported urinary quality life, based on (1) importance of the outcome to patients (Table 2) and (2) feasibility and rationale for evaluation in a phase 2 clinical trial. Oncological outcomes (eg, progression of disease) and complications were ranked highest by patients. However, progression and complications are rare and would require a very large study for adequate power. Discomfort was ranked third, and we considered this as the primary outcome. However, we felt that discomfort was too closely linked to the number of cystoscopy procedures that patients undergo in each arm. As such, this would clearly favor the urine testing arms, where patients undergo only two procedures instead of four scheduled procedures over the 2-yr study period (see the study schema in Fig. 1). For these reasons, oncological outcomes, complications, and discomfort were included as exploratory outcomes. Urinary quality of life 1–3 d after surveillance was ranked fourth and was chosen as the most meaningful and feasible primary outcome. For patients with a positive or nondiagnostic urine test, this outcome will be ascertained 1–3 d after the cystoscopy triggered by the urine test.

**Table 2 t0010:** Outcomes for the Replace Cysto trial

Rank	Outcome	How included in our study
1	Oncological outcomes, ie, not delaying detection of tumors	Exploratory outcome that will be assessed further in subsequent larger comparative effectiveness study if primary outcome is met
2	Complications of surveillance, eg, infections, strictures	Added as an exploratory outcome, not primary due to rarity of these events
3	Discomfort experienced after surveillance testing	Exploratory outcome, not primary as likely directly related to cystoscopy
4	Burden of surveillance, eg, urinary quality of life, anxiety	Primary outcome: urinary quality of life; exploratory outcome: anxiety
5	Number of cystoscopy procedures	Exploratory outcome

Rank indicates importance assigned by patients and caregivers, with “1” being most important. The five most important outcomes are shown out of a total list of nine reviewed with patients. These are previously unpublished data from workshopping the study with bladder cancer patients during the 2021 Bladder Cancer Advocacy Network’s Bladder Cancer Summit.

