The hypothesis tests of primary interest are whether urinary quality of life scores are improved 1–3 d after surveillance with urine testing relative to surveillance with frequent cystoscopy. For participants with a positive or nondiagnostic urine test, this outcome will be ascertained 1–3 d after the cystoscopy triggered by the urine test. Each of the two urine test modalities will be compared with the frequent cystoscopy arm, using the Bonferroni-Holm method [30] to control the family-wise type 1 error rate at 5%. Each of these two tests (each urine test vs frequent cystoscopy arm) will be conducted using a multivariate Wald test that averages the corresponding coefficients from the 6- and 18-mo time points from the interaction of the study arm with time points. If there is a significant effect of urine test modalities (done at 6 and 18 mo) compared with the frequent cystoscopy arm, we will test whether the effect is different at 6 versus 18 mo.

All analyses will be performed using intent-to-treat principles and within the intent-to-treat population. For example, if a patient in a urine test arm does not complete a urine test and has a cystoscopy instead at 6 or 18 mo, we will nonetheless analyze this patient’s outcome data from this time point as in a urine test arm.

We do not anticipate that missing data will be a major issue as each site will have at least one staff member dedicated to obtaining the primary outcome data, that is, validated urinary quality of life domain scores, 1–3 d after the surveillance visit. Based on a similar prior longitudinal study validating the QLQ-NMIBC24 [20], we assume 20% missing data for the primary outcome at each time point.

Missing outcomes can be analyzed as is using the mixed-effect model for longitudinal data described above, under the assumption that the distribution of the outcome in participants for whom it is not missing does not differ from the distribution in those in whom it is missing conditional on previous observations of the outcome and covariates. We will also carry out sensitivity analyses to determine to what extent conclusions are sensitive to departures from this missing at random assumption. Our longitudinal analytic approach described above allows us to incorporate study data even if study visits were missed or participants were lost to follow-up.

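### The Poisson model for procedure and complication counts borrows the primary outcome's arm-by-time structure, which does not suit near-fixed procedure counts or rare complications

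*Protocol article*

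**What the plan says.** Section 3.2.4 (Exploratory outcome analyses) treats complications and invasive procedures as counts over follow-up time, for example "the number of invasive procedures per time under surveillance". It assigns them "Poisson regression with a random intercept for each participant and the same fixed-effect model structure as described for the primary outcome".

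Section 3.2.2 (Primary outcome analyses) defines that structure: arm indicators, "time points (3, 6, 12, 18, and 24 mo) as categorical variables (3-mo baseline as referent"), "the interactions of the study arm and time point", and sex. The contrast tested for the primary outcome is one that "averages the corresponding coefficients from the 6- and 18-mo time points from the interaction of the study arm with time points".

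The Abstract names the exploratory quantity as "the number of invasive procedures that participants undergo per 1000 person years", and gives complications in the same unit. Section 2.3 describes the urine arms as those "where patients undergo only two procedures instead of four scheduled procedures over the 2-yr study period". It also calls complications rare, without giving a rate.

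**The concern.** The structure was built for a quality of life score that has a baseline value and is measured at every visit. Three things change when the outcome is a count.

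1. **Dispersion.** At a scheduled visit the number of procedures is about 1 in the cystoscopy arm and mostly 0 or 1 in a urine arm. Such counts vary less than Poisson counts with the same mean. A random intercept can only add variance, so the model cannot adapt and its intervals are too wide.
2. **Referent.** The 3-month cystoscopy is an eligibility condition (Sections 2.4 and 2.7) and precedes randomisation. As a baseline for procedures it carries no information.
3. **Sparsity.** Rare complications spread over 3 arms by 5 visits, that is 15 cells, will leave some cells empty. A log rate fitted to an empty cell has no finite maximum-likelihood estimate.

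The coefficients are also specific to visits and do not directly give the comparison of arms per 1000 person years named in the Abstract. Averaging only the 6- and 18-month terms leaves out the 12- and 24-month visits. At stake is the precision reported for the number of procedures, and whether the planned complication model gives an estimate at all. Patients ranked complications second and number of cystoscopies fifth in Table 2.

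**Working it through.** The article states no figure for these analyses, so there is none to reproduce.

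**Inputs from the article.** 80 participants per arm; Xpert sensitivity 0.72 and specificity 0.76; EpiCheck sensitivity 0.74 and specificity 0.84; recurrence 10% per year; attrition 10% per year (Section 3.1); withdrawal after recurrence or progression (Section 2.6.4); four scheduled cystoscopies against two plus triggered ones.

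**Assumptions, since the article gives no rates.** For-cause cystoscopy 0 to 0.3 per year; resection at recurrence counted or not; nondiagnostic test 0 or 5%; complications 0.5% to 10% per cystoscopy.

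**Step 1. Procedures by hand, simplest case.** Everyone is followed, with no recurrence and no for-cause procedures. A urine visit leads to cystoscopy with probability p = 1 − specificity: 0.24 for Xpert, 0.16 for EpiCheck. The control count and the 3-month count are both exactly 1.

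For the 6/18-month average minus the 3-month referent, urine arm minus control, on the log scale:

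- Poisson variance = 1/(2·80·p) + 1/(2·80) + 2/80.
- True variance = (1 − p)/(2·80·p), because the control and 3-month counts do not vary.

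| | Poisson variance | Poisson SE | True SE | Ratio |
|---|---|---|---|---|
| Xpert | 0.0260 + 0.0063 + 0.0250 = 0.0573 | 0.239 | √(0.76·0.0260) = 0.141 | 1.70 |
| EpiCheck | 0.0391 + 0.0063 + 0.0250 = 0.0703 | 0.265 | √(0.84·0.0391) = 0.181 | 1.46 |

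The 3-month referent alone adds 0.025 of variance that does not exist. Without it the ratios are 0.180/0.141 = 1.28 and 0.213/0.181 = 1.18.

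**Step 2. Procedures by simulation.** With recurrence, withdrawal and attrition added (24 scenarios, 2,000 trials each), model SE divided by true SE is:

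| Contrast | Xpert | EpiCheck |
|---|---|---|
| 6/18-month arm-by-time, 3-month referent | 1.55–1.85 | 1.30–1.62 |
| 6/18-month arm ratio, no baseline | 1.14–1.34 | 1.03–1.23 |
| Single overall person-time rate ratio | 1.88–3.22 | 1.88–3.39 |

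The full random-intercept Poisson likelihood was fitted to six simulated trials. The estimated random-intercept SD was 0.0025, effectively zero, in all six, so the random intercept corrects nothing. For an overall rate ratio in a further simulation of 600 trials (specificity 0.76, for-cause 0.1 per year), the empirical SD of the log ratio was 0.0372, the robust SE 0.0376 and the Poisson SE 0.0948.

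**Step 3. Referent.** If the 3-month cystoscopy is counted, the cell is 1 for every participant and adds only model-assumed noise (Step 1). If it is not counted, the cell is zero in all arms and no procedure interaction is estimable.

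**Step 4. Complications.** About 76 and 62 participants per arm reach the 6- and 18-month visits, and about 26% (Xpert) or 19% (EpiCheck) of urine visits lead to cystoscopy. At 5% per cystoscopy the expected counts are:

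- Xpert: 1.00 and 0.81.
- EpiCheck: 0.72 and 0.58.
- Control: 3.80 and 3.08.
- 3-month cells: 4.0 each (80·0.05).

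P(at least one of the six cells in a contrast is empty) = 1 − ∏(1 − e^(−λ)). For Xpert at 5%: 1 − 0.632·0.555·0.978·0.954·0.982² = 0.68. Repeating this at the other rates:

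| Complications per cystoscopy | Xpert | EpiCheck |
|---|---|---|
| 1% | above 0.99 | above 0.99 |
| 2% | 0.97 | 0.98 |
| 5% | 0.68 | 0.80 |
| 10% | 0.31 | 0.48 |

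These assume no complications after urine tests alone. Allowing 0.2% there gives 0.95/0.97 at 2%, 0.64/0.75 at 5% and 0.28/0.44 at 10%.

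**The case against.** **Exploratory and conservative.** Both outcomes are exploratory, and Section 3.1 says the trial is not adequately powered for complications. For procedures the error runs in the safe direction. With the log ratio of −0.46 from the 600-trial simulation, the Poisson interval is exp(−0.46 ± 1.96·0.0948) = 0.52 to 0.76, against 0.59 to 0.68 with the robust SE. Both exclude 1. This stands and limits the severity.

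**The unseen analysis plan.** Robust variance and sparse-data methods are commonly settled there, so their absence here is no fault. That also stands. The fixed-effect structure, however, is a stated choice. Robust variance would not repair the referent or the empty cells.

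**Parts of the remedy are implied.** Counting per time under surveillance suggests a person-time offset, and Section 2.6.2 refers to procedures during the study period, which points away from counting the eligibility cystoscopy. That is a fair reading, but it makes the 3-month referent cell empty, so the structure still cannot be carried over literally.

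**Complications are reported elsewhere.** A reader might infer that the trial would have no usable complication data. That does not follow. Section 3.3 tabulates adverse events per surveillance visit with binomial intervals, and crude rates per person-time need no regression. The tabulation is by type of surveillance performed, however, not by randomised arm.

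**A single rate ratio is not a stated target.** The article names no such estimand. It does name rates per 1000 person years, and the visit-specific interactions do not lead there directly.

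**Conclusion.** The point holds as a minor one. The prescribed model overstates the standard error for procedures by about 1.3 to 1.9 times for the 6/18-month arm-by-time contrast, given the article's test accuracy, recurrence and attrition and the assumed ranges above. Its 3-month referent has no sensible meaning for procedures. For complications, lack of a finite estimate is very likely at 2% or less per cystoscopy, more likely than not at 5%, and somewhat less likely than not at 10%.

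Two stronger readings are not supported. A reader might infer intervals about 2.5 times too wide. That size belongs to a single overall person-time rate ratio (range 1.9 to 3.4 across the assumed for-cause and resection rates), which the planned arm-by-time model does not contain. A reader might also infer that the complication coefficients are certain to be non-estimable, but that depends on a rate the article does not give. No primary result or stopping rule is affected.

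**What to change.** In Section 3.2.4, replace the reference to the primary outcome's fixed effects with a model for each participant's total post-randomisation count. It should have a log person-time offset, arm indicators and the stratification factors (site, sex, prior intravesical therapy). Leave out arm-by-time terms and the eligibility cystoscopy, and use robust (sandwich) variance. For complications, use the same model with exact or Firth-type inference if events are sparse. The result is a comparison of arms on the person-year scale of the Abstract.

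The cost is wording only, with no new data and no change in sample size. The downside is that visit-specific differences would be shown descriptively rather than estimated from the model.
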